**Fig. 1 Fig1:**
[figure not shown]
Overview of events across parallel sub-studies

Sub-study 1 involves four intervention groups: (1) normobaric hypoxia (12% O_2_) combined with cognitive training, (2) hypoxia (12% O_2_) with no training, (3) cognitive training under normoxia (20% O_2_), and (4) normoxia (20%) with no training in a double-blinded controlled design. This design enables us to disentangle combined and separate effects of altitude-like hypoxia and cognitive training. Participants are randomized in blocks and undergo interventions in these groups for practical reasons. During the three-week treatment, participants breathe 12% ambient oxygen (≈ 4400 m altitude) or approximately normal sea-level oxygen (20%) in a treatment room, 3.5 h daily, six days per week (18 sessions in total). After a blood test (days 1, 6, 20) and light standardized breakfast, they enter the treatment room. Here, they sit at a desk separated by desk dividers. On iPads, they perform cognitive training or matched control games without cognitive benefits. Cognitive training is interleaved by short breaks, during which the participants can relax or walk on a treadmill inside the room. This is to avoid complete physical inactivity throughout the 3.5 h sessions and thereby make the sessions more pleasant for participants. Participants undergo cognition assessments in weeks 1 (baseline), 4, and 8 and functional and structural MRI in weeks 1 and 8, when red blood cell counts are comparable between groups. Participants in the two extreme groups (normobaric hypoxia with cognitive training and normoxia with no training) will also undergo PET scanning in week 4 (post-treatment). Participants will be recruited consecutively for the PET scans until an equal distribution in each of the extreme intervention arms (i.e., hypoxia with cognitive training and normoxia with no training), sex, and age group is achieved.

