Sub-study 2 involves two intervention groups: (1) normobaric hypoxia (12%) combined with cognitive training 3.5 h daily, five to six days per week for three weeks (16 sessions in total), and (2) treatment as usual (TAU) in an assessor-blind controlled design. Patients in the TAU group will initially be assessed at the same time points as the active group with neurocognitive testing at baseline, week 4, and week 8, fMRI at baseline and week 8, and PET in week 4. After completed testing at week 8, patients in the TAU group undergo the three-week active intervention, followed by one additional neurocognitive assessment and mood rating in the week after treatment completion. The inclusion of this TAU arm rather than an active control group was chosen to ensure patient motivation and minimize attrition in this time-intensive study. Similar study designs with TAU control groups are common in pro-cognitive intervention studies investigating novel treatments in mood disorders and schizophrenia [39, 40]. Although patients will not be blinded to their allocated treatment arm, neurocognitive test results are generally not susceptible to placebo effects [41, 42] and assessments will be carried out by blinded, fully trained research assistants (psychology students).

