### Randomization and blinding

Randomization is conducted in the database program REDCap [51], which is also used to store the collected data, utilizing a 1:1 allocation ratio. Randomization occurs after inclusion of the participants planned to undergo treatment sessions together. Treatment groups are stratified for age (> 27 in sub-study 1 of generally young volunteers/ > 35 in sub-study 2 of patients). For randomization purposes, date of birth is registered to determine the stratum to which the participant belongs at the time of enrolment. Study identification numbers are given consecutively within each stratum and treatment arm. Randomization is conducted in the randomization module in REDCap, where an un-blinded researcher inputs the stratum and the program then retrieves the allocated intervention. To ensure blinding of the outcome-assessors, the randomization module in REDCap is only accessible to the researchers, who are not involved in evaluation of the efficacy parameters.

Healthy participants in sub-study 1 are blind to the oxygen condition since the low/normal oxygen air blown into the room is of equal temperature and humidity. Furthermore, they are told that they receive one of two forms of cognitive training, which effectively blinded participants in a previous study [52]. After study completion, we will assess whether blinding has been maintained for each participant, since there is a small risk that some participants develop symptoms of mild altitude sickness which could unblind them to their intervention. Blinding of the outcome assessors is ensured by their absence during the training visits (where oxygen levels are displayed and monitored on a screen outside the room). Participants will be instructed not to disclose any information concerning their intervention during outcome assessments and under no circumstances will the allocation be revealed to the outcome assessors. The training visits are conducted by researchers who are not involved in outcome assessments.

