### Statistical analyses

#### Primary, secondary, tertiary, and exploratory outcome measure analyses

Behavioral data from neuropsychological test score performance, subjective cognitive impairments, quality of life, level of functioning, psychosocial functioning, and mood symptoms (i.e., data from the primary, secondary, and tertiary outcomes) will be analyzed using mixed model design. Hence, the analyses investigate how the mean score of each outcome changes over time in each treatment group and testes for interaction effects (i.e., are the trajectories different between the groups). All analyses will be based on an intention-to-treat (ITT) principle. Hence, all participants will be analyzed based on their allocated intervention arm. Participants with incomplete data will also be included in the analyses without any ad hoc imputation [71]. No interim analyses will be performed. A nonblinded researcher will pseudo-anonymize the data prior to analysis, and data analyses will thus be conducted by blinded researchers.

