### Data management and monitoring

All personal information will be obtained at the eligibility assessment or from patient records in cases where participants are unable to provide the needed information. Pseudo-anonymized data from the neuropsychological tests, virtual reality test, questionnaires, interviews, and functional assessment will be registered in the REDCap database, which meets requirements from the Danish Data Protection Agency. Pseudo-anonymized raw paper data from neuropsychological tests are kept in a locked filing cabinet. Questionnaires and interviews are collected directly in REDCap. Data quality is ensured by score range restrictions on values for all outcomes, and all data for the primary and secondary outcome measures will be doublechecked prior to analyses. Signed consent forms as well as a list that matches participant ID numbers with personal information are kept separate from pseudo-anonymized data. The key matching participants’ personal information with their ID number will be deleted and consent forms maculated 10 years after study completion. At this point, all data will be completely anonymized. All trial authors will have access to the final trial dataset. If a participant is excluded or withdraws from the study, the reason for exclusion is documented in REDCap, along with information regarding any adverse events.

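### Study IDs are numbered within treatment arm, so an ID visible to outcome assessors could reveal the allocation, most seriously in sub-study 2

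*Protocol article*

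**What the plan says.** The numbering rule is in the Randomization and blinding section of the protocol article: "Study identification numbers are given consecutively within each stratum and treatment arm". The same section sets out how outcome assessors are kept blind:

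- the REDCap randomization module is closed to them;
- they are absent from training visits, which other staff run;
- participants are told not to talk about their intervention;
- "under no circumstances will the allocation be revealed to the outcome assessors".

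On record keeping, the Data management and monitoring section says "Pseudo-anonymized raw paper data from neuropsychological tests are kept in a locked filing cabinet". It adds that neuropsychological data also go into REDCap in pseudo-anonymized form, and that a separate list links ID numbers to personal details.

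For analysts, the Statistical analyses section has a nonblinded researcher pseudo-anonymize the data first, and concludes that "data analyses will thus be conducted by blinded researchers".

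Sub-study 2 compares hypoxia cognition training with "treatment as usual (TAU) in an assessor-blind controlled design". The Study design and procedure section accepts that patients are not blind and relies on blinded research assistants for the assessments.

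**The concern.** A number that runs consecutively within an arm can be issued only once the arm is known. For such numbers to be unique across arms, they need separate ranges or prefixes, and those track the allocation. Closing the randomization module to assessors does not help if the label on the form carries the same information.

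At stake is the blinding of the primary outcome. The composite includes word-list recall, verbal fluency and letter-number sequencing, where an examiner's administration and scoring matter. In sub-study 2 the patient knows the arm, so the assessor is the only blinded party at the point of measurement.

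**Working it through.** The article states no figure on this point, and the point does not depend on alpha, power or effect size. The check is a count of the ID series that the rule creates, followed by tracing what one disclosure reveals.

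**Inputs**

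- Arms: "Sub-study 1 involves four intervention groups"; sub-study 2 has two arms (Study design and procedure).
- Strata: one age cut-point per sub-study, hence two strata each: "Treatment groups are stratified for age (> 27 in sub-study 1 of generally young volunteers/ > 35 in sub-study 2 of patients".
- Allocation: "utilizing a 1:1 allocation ratio".
- Planned size: 120 healthy participants and 60 patients (Sample size and power calculation).

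**Number and size of series** (series = arms × strata; mean size = N ÷ series)

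- Sub-study 1: 4 × 2 = 8 series; 120 ÷ 8 = 15 participants on average.
- Sub-study 2: 2 × 2 = 4 series; 60 ÷ 4 = 15 patients on average.

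**What one known allocation reveals, if the series can be told apart**

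- Sub-study 1: its own series, about 15 participants. Three other arms remain possible for the rest of that stratum.
- Sub-study 2: its own series and, because there are only two arms, the other series in that stratum by elimination. With equal strata this is 15 + 15 = 30 patients.

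**How easily one disclosure could arise in sub-study 2.** The documents give no rate for a patient letting the arm slip, so I assume a per-patient chance p, independent between patients, and show a range. The chance of at least one slip among 30 patients is 1 − (1 − p)^30:

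| Assumed p | Chance of at least one slip among 30 |
|---|---|
| 1% | 1 − 0.99^30 = 26% |
| 5% | 1 − 0.95^30 = 79% |
| 10% | 1 − 0.90^30 = 96% |

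**A route that needs no slip.** In sub-study 2 only treatment-as-usual patients receive the intervention after week 8 and return for the additional assessment (Study design and procedure; week-12 column of Table 1). Whoever conducts or sees a week-12 record knows that this ID belongs to the treatment-as-usual arm. With arm-neutral IDs, this reveals one patient whose week-4 and week-8 outcomes are already complete, which is harmless. With arm-ordered IDs, it can identify the series, including patients not yet tested. The article does not say who performs the week-12 visit, and nothing in it excludes the same assessors.

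**Safeguards against the gap.** Module access, absence from training visits, separate training staff and the non-disclosure instruction each block a different channel. None mentions the ID.

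**The case against.** The strongest reply is that the essential links are inferred. The article gives no ID format and does not say that the arm-ordered number is what assessors see. It also implies that another identifier may exist. Consent, eligibility, SCIP and mood ratings come before the intervention, and randomization follows inclusion. An arm-dependent number cannot label data recorded before allocation, and assessors may keep using the number that does. Which identifier stands on which form is also a detail that an article may leave to the full protocol. This stands as a limit on the claim and makes it conditional. It does not remove the point, because the numbering rule is itself stated and runs against the blinding that the same section promises.

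Three stronger readings are tempting, and the documents do not support them.

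- A reader might infer that the analysts are unblinded too. The article has a nonblinded researcher pseudo-anonymize the data before analysis. As the test data are already held in pseudo-anonymized form, this can reasonably be read as a recoding. It protects analysts if it replaces the study ID. The text does not say whether it does, so this is a point to confirm.
- A reader might take the article's remark on altitude symptoms as a trigger. That remark concerns sub-study 1 participants guessing their own condition. An assessor would learn of it only if the participant broke the non-disclosure instruction. Sub-study 1 participants are also blind to oxygen and are told that they receive one of two forms of training, so most could not name their arm.
- A reader might infer that all 180 participants (120 + 60) are exposed, or attach a bias in SD units to the composite. One disclosure reaches one series, or one stratum in sub-study 2. Nothing in the documents supports a size for scoring bias, and RVP speed, one of the six components, comes from a computerized battery.

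**Conclusion.** The numbering rule makes the study ID depend on the allocation, and no stated assessor safeguard covers the ID. This is a gap in the protection of blinding; the other safeguards remain in force, and the article does not show that anyone has been unblinded.

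Its reach per disclosure is about 15 participants on average, and about 30 in sub-study 2. These sizes assume that IDs are unique within a sub-study, that the series can be distinguished, that assessors see the ID and, for the figure of 30, that the age strata are of equal size. The point carries most weight in sub-study 2, for the reasons given above. It merits correction because a stated rule needlessly endangers the assessor blinding on which that comparison rests.

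**What to change.** 1. Issue study IDs in a single enrolment-order sequence, before randomization and independent of arm. Keep the allocation only in the REDCap randomization module.
2. For participants already numbered by arm, use an arm-neutral alias on all remaining assessor-facing sheets and forms, including the week-12 records.
3. Confirm in the text that the pseudo-anonymization before analysis replaces the arm-ordered ID.
4. If assessors already work with a different, arm-neutral identifier, say so. That would settle the assessor part.

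The cost is small: a numbering setting, and an alias list that the unblinded researcher keeps and reconciles across paper and REDCap. By April 2024, 62 + 33 = 95 participants were included (Trial status and dissemination), so the reconciliation is real work. At that date 120 − 62 = 58 healthy participants and 60 − 33 = 27 patients were still to be included and could be numbered neutrally from the start. Sample size, power, alpha and outcomes are unchanged.

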### Intervention: hypoxia cognition training

#### Low/normal ambient oxygen

Fresh air with 12% or 20% O_2_ is blown into a sealed 20 m^3^ room by a 4 kW air compressor with a safety-approved system developed by HöhenBalance, Austria (see Fig. 2 for experimental setup). For the active condition, participants enter the room at 16% O_2_ (≈ 2,200 m altitude). Upon entry, the O_2_ levels will be reduced from 16 to 12% (≈ 4400 m altitude) in a 30-min lead-in phase. The precise control by the HöhenBalance systems allows control of O_2_ levels to ± 0.1%. The target O_2_ level of 12% will be maintained over three hours.

**Fig. 2 Fig2:**
[figure not shown]
Experimental setup

HöhenBalance systems create simulated altitude by introducing normobaric breathable hypoxic air. Therefore, even under any conceivable worst-case failure condition, the systems cannot give rise to any potentially harmful oxygen condition to persons inside or outside the room. A password access control provides additional safety.

#### Cognitive training and matched computer games

The web-based cognitive training (Happy Neuron Pro) is grounded on principles of neuroplasticity-based learning by being intensive, neuroadaptive, engaging, and rewarding. This web-based training program has been translated into Danish and is used for traumatic brain injury, schizophrenia, and in our previous cognitive remediation trial ([53] and www.happyneuronpro.com), making its implementation feasible. Participants in the no training control condition receive computer games similar to Happy Neuron Pro but with low cognitive demand that produce no cognitive benefits [52]. Specifically, this sham procedure involves the exact same stimuli as the active condition but with changes from trial to trial only in the appearance of the tasks. In contrast, the active training involves parametric task adjustment by decreasing stimuli presentation time, increasing working memory load, decreasing time to respond, and increasing the number of non-target items (distractors).

### Outcome measures

For an overview of outcome assessment domains, measures, frequency, and timing, see Table 1. The outcome measures listed below are consistent with the latest recommendations from the International Society for Bipolar Disorders (ISBD) Task Force [54].

**Table 1 Tab1:** Schedule of enrolment, interventions, and assessments

**Timepoint**	**Pre-intervention**	**Baseline (week 0)**	**Active treatment phase**	**End of treatment (week 4)**	**Follow-up (week 8)**	**Additional end of treatment assessment (week 12)** For sub-study 2 TAU group
**Enrolment**						
Project information: written/oral communication	x					
Written informed consent	x					
Eligibility assessment	x					
Randomization	x					
**Intervention and safety outcomes**						
Repeated moderate hypoxia exposure or normoxia (3.5 h per day, five to six days per week for three weeks)			x			
Cognitive training or sham training (3.5 h per day, five to six days per week for three weeks)			x			
Blood sampling (blood counts)	x	x	x (days 1, 8, and 19)	x	x	
Safety monitoring and assessments of potential adverse events		x	x	x	x	/
Mood ratings (HDRS + YMRS)	x	x		x	x	/
ESQ			x			
VAS			x			
**Cognitive measures**						
RAVLT		x		x	x	/
TMT-A		x		x	x	/
TMT-B		x		x	x	/
RBANS Coding		x		x	x	/
RBANS Digit Span		x		x	x	/
WAIS-III LNS		x		x	x	/
RVP		x		x	x	/
SWM		x		x	x	/
OTS		x		x	x	/
ERT		X		x	x	/
Verbal fluency (S + D)		x		x	x	/
SDMT		x		x	x	/
WCST		x		x	x	/
**Functioning measures**						
FAST		x			/	
CAVIR		x			x	/
**Self-report measures**						
AQoL		x		x	x	/
COBRA		x		x	x	/
SDS		x		x	x	/
WHOQOL-BREF		x		x	x	/
WSAS		x		x	x	/
PSQI		x		x	x	/
**Neuroimaging**						
sMRI + fMRI		x			x	
PET (a subgroup of the participants)				x		
**Other measures**						
DART		x				
CTQ	x					
SCIP	x					
Research biomarker blood samples			x (days 1 and 19)			

x = included in both sub-studies. / = included in sub-study 2 only

*Abbreviations*: *HDRS* Hamilton Depression Rating Scale, *YMRS* Young Mania Rating Scale, *ESQ* Environmental Symptoms Questionnaire, *VAS* visual analogue scale, *RAVLT* Rey Auditory Verbal Learning Test, *TMT-A* Trail Making Test Part A, *TMT-B* Trail Making Test Part B, *RBANS* Repeatable Battery for the Assessment of Neuropsychological Status, *WAIS-III LNS* Wechsler Adult Intelligence Scale version 3 Letter-number-sequencing, *RVP* Rapid Visual Information Processing (CANTAB, Cambridge Cognition Ltd.), *SWM* spatial working memory (CANTAB, Cambridge Cognition Ltd.), *OTS* One Touch Stockings of Cambridge (CANTAB, Cambridge Cognition Ltd.), *ERT* Emotion Recognition Task (CANTAB, Cambridge Cognition Ltd.), *SDMT* Symbol Digit Modalities Test, *WCST* Wisconsin Card Sorting Test, *Connor’s CPT* Connor’s Continuous Performance Test, *FAST* Functional Assessment Short Test, *CAVIR* Cognition Assessment in Virtual Reality test, *AQoL* Assessment of Quality of Life, *COBRA* Cognitive Complaints in Bipolar disorder Rating Assessment, *SDS* Sheehan Disability Scale, *WHOQOL-BREF* World Health Organization Quality Of Life, *WSAS* Work and Social Adjustment Scale, *PSQI* Pittsburgh Sleep Quality Index, *fMRI* functional magnetic resonance imaging, *PET* positron emission tomography, *DART* Danish Adult Reading Test, *CTQ* Childhood Trauma Questionnaire, *SCIP* Screen for Cognitive Impairment in Psychiatry (Danish version)

#### Primary outcome measure

The primary outcome measure is changes in a cognitive composite score, consisting of neuropsychological tests covering attention, memory, and executive functions from baseline to week 4. We have previously demonstrated an improvement on this *speed of complex cognitive processing* composite measure in patients with BD after 8 weeks of EPO treatment [28]. In the present trial, the specific tests included in the primary composite outcome measure are the Rey Auditory Verbal Learning Test (RAVLT) [55], The Repeatable Battery for the Assessment of Neuropsychological Status (RBANS) Coding [56], Verbal Fluency with the letter “D” [57], Wechsler Adult Intelligence Scale (WAIS)-III Letter-Number Sequencing [58], Trail Making Test Part B (TMT-B) [59], and Rapid Visual Information Processing (RVP) from the Cambridge Neuropsychological Test Automated Battery (CANTAB, Cambridge Cognition Ltd.). To derive the cognitive composite score, we will z-transform and sum performance scores from RAVLT total recall, TMT-B, WAIS-III Letter-Number Sequencing, RBANS Coding, Verbal Fluency (letter “D”), and RVP speed for correct responses [28].

#### Secondary outcome measures

The secondary cognitive outcome measure consists of mean choices to correct in the One Touch Stockings of Cambridge (OTS) test from CANTAB, which yielded particularly strong effects of cognitive training with Happy Neuron in our previous study [60]. Dorsal prefrontal cortex (dPFC) activity during spatial working memory (N-back task) is another secondary outcome measure because the dPFC is consistently engaged in both healthy participants and patients with mood disorders in response to successful pro-cognitive interventions [61].

Additionally, sub-study 2 of patients with mood disorder includes a measure of daily functioning as secondary outcome in accordance with the ISBD recommendations [54]. The effect of the intervention on daily functioning is assessed with a novel virtual reality test of daily life cognitive skills, the Cognition Assessment in Virtual Reality (CAVIR) test [62]. The CAVIR test is an engaging, immersive, and self-administered 360° VR test in a kitchen, where the participant’s cognitive skills related to planning and preparing a meal are assessed, thus enabling insight into patients’ daily life cognitive skills.

#### Tertiary outcome measures

The tertiary cognitive outcome measures are the RAVLT, RBANS Coding and Digit Span, Verbal Fluency with the letters “S” and “D”, WAIS-III Letter-Number Sequencing, the Wisconsin Card Sorting Task (WCST), the Rapid Visual Information Processing (RVP; CANTAB), additional measures from the One Touch Stockings of Cambridge (OTS; CANTAB), the spatial working memory (SWM; CANTAB), and the Emotion Recognition Test (ERT; CANTAB), as well as the Trail Making Test Part A (TMT-A) and B (TMT-B), respectively.

The Assessment of Quality of Life (AQoL) [63], the Cognitive Complaints in Bipolar Disorder Rating Assessment (COBRA) [47], Sheehan Disability Scale (SDS) [64], the World Health Organization Quality of Life (WHOQOL-BREF) [65], the Work and Social Adjustment Scale (WSAS) [66], and the Pittsburgh Sleep Quality Index (PSQI) [67] will be applied. Finally, psychosocial functioning is also assessed with the clinician-rated interview Functional Assessment Short Test (FAST) [68]. History of early life stress will be assessed with the Childhood Abuse and Trauma Scale [69] at the time of inclusion.

To minimize learning effects on neuropsychological test with repeated testing at the follow-up assessments, alternate versions of the RAVLT (original list AB, GeAB, and Cr-AB) and RBANS Coding and Digit Span (version A and B) are used. These versions are administered in counter-balanced order within each stratum. Finally, premorbid verbal IQ is assessed with the Danish Adult Reading Test [70].

